**Table 1: Lifestyle questionnaire.**

| Physical Activity                          | +1 | 0 | 1 | +1, 0 or -1 |
|----------------------------------------------------------|------------------|-----------------|-----------------|---------------------------|
| Walking daily                                            | + 1 h            | 30-60 min.      | - 30 min        |                           |
| Climbing stairs (daily)                                  | + 16             | 4-16            | - 4             |                           |
| At least 30 min of more than moderate intensity (weekly) | + 3              | 1-3             | - 1             |                           |

| Weekly consumption              | +1 | 0 | 1 | +1, 0 or -1 |
|-----------------------------------------------|------------------|-----------------|-----------------|---------------------------|
| Vegetables and salads                         | + 12             | 6-12            | - 6             |                           |
| Pieces of fruit                               | + 12             | 6-12            | - 6             |                           |
| Nuts                                          | + 3              | 1- 3            | - 1             |                           |
| EVOO                                          | + 6              | 3 - 6           | - 3             |                           |
| Oily fish and iberian ham                     | + 3              | 1 - 3           | - 1             |                           |
| Wholegrain cereals                            | + 6              | 3 - 6           | - 3             |                           |
| Legumes                                       | + 2              | 1 - 2           | - 1             |                           |
| Skimmed dairy                                 | + 6              | 3-6             | - 3             |                           |
| Red and processed meats                       | - 3              | 3-6             | + 6             |                           |
| Sauces (except mayonnaise, ali oli with EVOO) | - 2              | 2- 4            | + 4             |                           |
| Sugary drinks (includes juices)               | - 2              | 2 - 4           | + 4             |                           |
| Cookies and ready-sliced bread                | - 2              | 2- 4            | + 4             |                           |

A physician with expertise in clinical and research activities focused on diabetes physiopathology, complications and prevention will be responsible to obtain fasting blood samples to determine HbA1c, lipid profile,  $\gamma$ -tocopherol levels (to confirm compliance in the group receiving pistachios), as well as a first-morning urine sample for the analysis of albumine-to-creatinine ratio and hydroxytyrosol levels (to confirm compliance in the group receiving EVOO). The physician will be also responsible to recollect clinical and lifestyle data from all women.

[name] will manage the global project and will develop a program for institutional relations.

## **STATISTICAL ANALYSIS**

Analysis of all the variables pertaining to efficacy will be performed on an intention-to-treat basis, including data on all patients randomized and all available follow-up data.

The Student's t test or ANOVA [nonparametric test (RANK TEST)] will be used to compare continuous variables [and expressed as means standard deviation (SD)] while categorical variables will be compared using the chi-squared test. The association between qualitative variables will be analyzed by the chi-squared test or Fisher's exact test in case more than 25% of the expected values will be less than five. In the case of ordinal variables, the hypothesis of ordinal proportion tendency will be tested.

Relative risk will be assessed together with its 95% confidence interval, using Cornfield's method. In all cases, the distribution of the variable versus the theoretical models will be checked, and the variance homogeneity hypothesis will be tested. The paired Student's t test or a repeated measures analysis of variance (MANOVA) will be used to compare continuous variables. The changes in variables with time (pre- and post-treatment) will be estimated by a MANOVA. Variables included will be treatment and study period. Mathematical models will be chosen by the type of variable and used logistic analysis, linear regression or Cox regression. The existence of interactions will be evaluated. Variables showing a p value under 0.15 in the univariate analysis will be selected for the multivariate analyses. The null hypothesis will be rejected in each statistical test when  $p < 0.05$ . Analysis will be performed using windows SPSS version 17.0 software and STATA 12.

Interim analyses: No applicable.

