### **SAMPLE SIZE CALCULATION**

For sample size calculation, a primary end-point for conversion to GDM has been used, assuming an expected conversion rate of 35% between 24-28 GWs and a reduction of at least 30% in the conversion to GDM after intervention. This intervention has shown a decrease of FPG -7 (-13; -1.3) mg/dl after 3 months in the PREDIMED Study (1), representing a potential reduction of GDM rate higher than 30%. A sample size of 315 women analyzed per group to provide statistical power of 80% to detect a 30% difference between groups in the primary outcomes at 5% significance. This number has been increased to **500 per group**, to allow for a predicted drop-out of around 20% (in accordance with the expected response rate, loss to follow up, lack of compliance, and any other predicted reasons for loss of subjects). Therefore, **1000 women will be randomized** in the study and we expect to assess at least 700.

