## Final statistical analysis

### Sample size

For sample size calculation the primary end-point was the incidence of GDM between 24-28 GWs. We estimated that 315 women per group would be required to provide statistical power of 80% (2-tailed  $\alpha = 0.05$ ) to detect a relative risk reduction of at least 30% after intervention assuming an incidence of 35% GDM in the control group. Previously, this intervention has shown a decrease of the median of fasting blood glucose (FBG) -0.38 mmol/L after 3 months, representing a potential reduction of GDM rate higher than 30%. Taking into account loss to follow-up, we included 1000 successive women that attended their first ultrasound visit at the Obstetrics department between 12-14 GW, to guarantee a minimum duration of 12-weeks of intervention.

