### Statistical analysis.

Variables are presented with their frequency distribution. Quantitative variables are summarized by their mean and standard deviation ( $\pm$ SD). All primary analyses were performed on an intention-to-treat basis. Comparison between baseline group characteristics and primary and secondary outcomes for qualitative variables were evaluated by the chi-squared test. For quantitative variables, measures were compared through Student's t test or the nonparametric Mann-Whitney U test if the quantitative variables would not adjust to a normal distribution. The Shapiro-Wilk test was used to verify the normal distribution of data.

Logistic regression analyses were used to assess the effect of the intervention for the primary and secondary outcomes that were significantly different in the univariate analysis. The magnitude of association was evaluated using the odds ratio (OR) and 95% confidence interval (CI). A crude and 5 multivariate models were fitted: model 1 was adjusted for age (continuous) ethnicity and parity; model 2 adjusted for pregestational BMI and gestational weight gain (continuous); model 3 adjusted for gestational, personal and family history, and smoker status (never, current, or former smoker); Model 4 adjusted for the variables in Models 1 and 2; and Model 5, adjusted for the variables in Models 1-3. These models 4 and 5 were only fitted for the primary outcome due to the small number of events in many of the secondary outcome variables.

All *p* values are 2-tailed at less than 0.050. Analyses were done using SPSS, version 21 (SPSS, Chicago, Illinois).

ADENDUM April 01, 2017.

Statistical analysis.

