At the suggestion of the statistic ([name]) the crude relative risk has been estimated for each outcome of interest and different methods have been tested for the estimation of adjusted relative risks in cohort studies and clinical trials of common outcomes (1,2,3): a method proposed by Zhan and Yu (2) to correct the adjusted odds ratio in cohort studies of common outcomes and estimate adjusted relative risk and its confidence interval when the incidence of disease is common and adjust for confounding variables exist; the log-binomial model (one of the criticisms of using the log-binomial model for the RR is that it produces confidence intervals that are narrower than they should be, and another is that there can be convergence problems; in our case we have problems of convergence to provide parameter estimates); Poisson regression with robust error variance and Cox regression with robust variance to obtain corrected confidence intervals.

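### The original plan gives the relative risk an odds-ratio (Cornfield) interval, and the later sections never settle which effect measure or adjusted model is primary

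*Protocol*

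**What the plan says.** Four places in the Protocol bear on the effect measure for the primary outcome, gestational diabetes (GDM) at 24-28 weeks.

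- **Sample size** (under Final statistical analysis): the trial is sized "to detect a relative risk reduction of at least 30% after intervention assuming an incidence of 35% GDM in the control group". That is a relative-risk scale.
- **Statistical Analysis** (original plan): "Relative risk will be assessed together with its 95% confidence interval, using Cornfield's method". The sentence is general and does not name the primary outcome, but the section gives no other interval for a relative risk.
- **Statistical analysis** (under Final statistical analysis): "The magnitude of association was evaluated using the odds ratio (OR) and 95% confidence interval (CI"). This comes from one crude and five adjusted logistic models, none named as primary. Model 2, and so Models 4 and 5, adjust for gestational weight gain.
- **Addendum of April 01, 2017**: a crude relative risk has been estimated for each outcome, and "different methods have been tested for the estimation of adjusted relative risks in cohort studies and clinical trials of common outcomes". Those listed are the Zhang-Yu correction of the odds ratio, the log-binomial model, Poisson regression with robust variance and Cox regression with robust variance. Of the log-binomial model it says "in our case we have problems of convergence to provide parameter estimates".

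Both analysis sections compare categorical outcomes by the chi-squared test.

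**The concern.** Two things are wrong. First, the original plan pairs a relative risk with a method that yields odds-ratio limits. When about a third of controls have the outcome, the two scales are far apart, and the mismatched interval lies further from 1 than it should.

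Secondly, the later text does not repair this. It moves to the odds ratio and then partly back to the relative risk. It does not say that one replaces the other, which adjusted method is kept, or which covariate set is primary. The addendum's remark on convergence shows that models had been run on trial data while this was open. At stake are the size and precision of the reported benefit, not whether the crude null hypothesis is rejected.

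**Working it through.** **Inputs.** Control risk 35% and relative risk reduction 30% (Sample size), so the intervention risk is 0.70 × 0.35 = 0.245. Power 80%, two-tailed 5% level. Allocation 1:1. 315 per group required; 500 per group randomised; at least 700 women, or 350 per arm, expected to be assessed (Sample Size Calculation).

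**Step 1: the plan's own figure.** With mean risk 0.2975 and difference 0.105,

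n = [1.96·√(2 × 0.2975 × 0.7025) + 0.8416·√(0.35 × 0.65 + 0.245 × 0.755)]² / 0.105² = 296.4.

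With continuity correction, (n/4)·[1 + √(1 + 4/(n × 0.105))]² = 315.2. The stated 315 therefore reproduces (316 if rounded up), on the relative-risk reading of the 30%.

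**Step 2: the two measures at the design rates.** RR = 0.245/0.35 = 0.70. OR = (0.245/0.755)/(0.35/0.65) = 0.603. A 30% lower risk is a 40% lower odds.

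**Step 3: the two intervals at 315 per arm.** Expected events are 77.175 and 110.25.

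- Relative risk: SE of log RR = √(1/77.175 − 1/315 + 1/110.25 − 1/315) = 0.1252. The limits are 0.70·exp(±1.96 × 0.1252) = 0.548 to 0.895.
- Cornfield, without continuity correction: hold the margins fixed (187.425 events in all) and find the intervention counts x that satisfy |77.175 − x| = 1.96·[1/x + 1/(315 − x) + 1/(187.425 − x) + 1/(127.575 + x)]^(−1/2). The solutions are x = 66.31 and 88.41. The odds ratio at x is x(127.575 + x)/[(187.425 − x)(315 − x)], which gives 0.427 and 0.851.

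**Step 4: the range of sample sizes.** Coverage is the share of 400,000 simulated trials per row, at the design rates, in which the odds-ratio interval contains 0.70. The simulation used Woolf limits, which agree with Cornfield to within 0.001 on these tables.

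| Per arm | RR interval | Cornfield (OR) interval | Coverage of RR 0.70 by the OR interval | Upper limit below 0.70 |
|---|---|---|---|---|
| 315 | 0.548-0.895 | 0.427-0.851 | 86.6% | 13.2% |
| 350 | 0.555-0.884 | 0.434-0.836 | 85.6% | 14.2% |
| 500 | 0.576-0.851 | 0.458-0.793 | 81.3% | 18.6% |

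The log-RR interval covers 0.70 in about 95.1% of trials in each row. Nearly all misses of the odds-ratio interval are on the side that exaggerates benefit, and coverage worsens as the trial grows.

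**Step 5: the adjusted methods.** These need not agree. In an illustrative simulation of 1,500 trials (assumed: 400 per arm, one prognostic covariate with log-odds 0.7 per SD, true RR 0.70), the median estimates were 0.70 for the crude RR, 0.70 for robust Poisson, 0.68 for Zhang-Yu and 0.58 for the adjusted odds ratio. The log-binomial fits were unreliable and are not used.

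**The case against.** The strongest reply is that these are successive layers, not rivals: an original plan, a section headed as final, and a dated addendum. The Cornfield sentence sits in the oldest layer and the final section does not repeat it. That is a reasonable reading, but the Protocol never says that the older text is withdrawn or that the relative risk displaces the odds ratio. The original sentence is wrong as worded in any case.

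Several stronger readings go too far.

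- *That the final section passes off an odds ratio as a relative risk, so that 30% is reported as 40%.* It labels the odds ratio correctly, and the addendum moves to relative risks because the outcome is common. Mislabelling is confined to the Cornfield sentence.
- *That the primary test is open to choice.* The chi-squared test is the same in both sections. In a crude simulation at 315 to 500 per arm, odds-ratio and relative-risk intervals agreed on significance in at least 99.7% of trials.
- *That every estimate is open.* The crude relative risk is stated plainly. The four methods concern only the adjusted one, and log-binomial is reported as having convergence problems.
- *That a method was picked for its result.* The wording shows that methods were run on trial data. It does not show which was reported or why, nor whether the analyst was unblinded, and the addendum discloses the trial of methods openly.
- *That the Zhang-Yu interval inflates the benefit.* Applied to a crude odds ratio at an assumed 400 per arm, its coverage was about 96.3%, slightly conservative. The Protocol applies it to adjusted odds ratios, which that check does not measure.

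**Conclusion.** The concern holds in limited form. The Cornfield rule is an error as written: at the design rates and 315 per arm it would put about 0.427 to 0.851 around a relative risk of 0.70, in place of 0.548 to 0.895. Taken as a relative-risk interval, it covers the true value about 81% to 87% of the time over 500 to 315 per arm. In addition, no section names one primary effect estimate, one adjusted method or one adjustment set, although the sizing is on the relative-risk scale.

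The figures rest on the Protocol's assumed 35% and 24.5%. At a lower control risk the two scales lie closer: for RR 0.70 and a 12.5% control risk, the odds ratio is 0.67. The sample size and the crude chi-squared test are not affected. A separately written analysis plan, if one exists, would not remove the conflict within this document, which carries its own final analysis section and addendum.

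**What to change.** 1. Replace Cornfield's method with an interval that belongs to the relative risk (log-RR or robust Poisson).
2. State that the relative risk replaces the odds ratio as the primary effect measure, with the crude relative risk and its 95% interval as the primary estimate, alongside the existing chi-squared test.
3. Name one adjusted model: Poisson regression with robust variance, which the addendum already lists, with baseline covariates only. Leave out gestational weight gain, which arises after randomisation and may itself be changed by the diet.
4. Keep the odds ratio, Zhang-Yu and other results as labelled sensitivity analyses. Do not delete analyses already run.
5. State that the adjusted method was chosen after the data had been seen.

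The cost is wording and a re-labelling of output. No new data are needed and 315 per group stands. The downside for the sponsor is that the headline effect looks smaller than the odds ratio (0.70 against 0.60 at the design rates).

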### ***Follow-up***

Women will be enrolled at 8-12 GWs (visit 0) and will follow-up at GWs 12-14 (visit 1), 24-28 (visit 2), 34-36 (visit 3) and delivery (visit 4), as well as at 12 weeks (visit 5) and 1 year post delivery (visit 6).

Baseline assessments (Visit 0): Women will be evaluated after the signature of the informed consent form. A complete medical history and physical exam will be performed. Subsequent assessments (Visits 1-6): Women will be followed up by means of clinic visits by the study staff. Six clinic visits will be performed, including: assessment of endpoints/outcome measures, assessments of safety including general (e.g. physical examination), specific safety assessments (e.g. blood chemistries including general biochemistry, hematology and urine analyses) and adverse event collection, assessment of compliance with the study and recording of concomitant medications. Blood and stool samples will be taken at this time. At visit 5 and 6, cord blood and placenta will be taken.

All biological samples will be extracted in one point and will be supervised by a scientist staff that will ensure fit for-purpose operations (high-throughput, high-quality). Design and testing of the sample-handling protocol will consider key factors that could affect the stability of biological samples, including anti-coagulants, stabilizing agents, temperature, and elapsed time from collection to initial processing and endogenous

degrading properties (enzymes). Sample fractions will be stored in two separated ultra-low temperature freezers to ensure long-term stability and integrity.

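### For repeated continuous secondary outcomes, the stated MANOVA in its classical form drops women with a missing visit, against the plan's own data rule, and the treatment contrast is not named

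*Protocol*

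**What the plan says.** The Protocol's Statistical Analysis section opens with an intention-to-treat rule, "including data on all patients randomized and all available follow-up data". For repeated measurements it offers a paired t test or a repeated-measures analysis of variance, labelled MANOVA, and continues: "The changes in variables with time (pre- and post-treatment) will be estimated by a MANOVA. Variables included will be treatment and study period". A little later comes a general sentence, "The existence of interactions will be evaluated", which is tied to no model or factor. The software is named (SPSS and STATA), but not the routine.

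The outcomes concerned are in the secondary list under Objectives: changes in HbA1c, insulin, HOMA, lipids, body weight, blood pressure and adherence. Follow-up schedules visit 0 (8-12 gestational weeks), visits 1 to 4 up to delivery, "as well as at 12 weeks (visit 5) and 1 year post delivery (visit 6"). The lifestyle session is held at visit 1 (Team). Under the November 2014 addendum the oil and pistachios are also supplied then.

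On loss, Sample Size Calculation predicts drop-out of around 20% and adds "we expect to assess at least 700", out of 1000 randomised.

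The later Final statistical analysis section compares quantitative variables by t test or Mann-Whitney test. It neither mentions MANOVA nor withdraws it.

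**The concern.** Two things do not fit together.

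First, classical repeated-measures MANOVA needs a complete vector for each woman over the visits entered. A woman with one of those values missing is removed from all of them, including visits she attended. That conflicts with the rule in the same section that all available follow-up data are used. A complete-case analysis is also generally valid only if loss is unrelated to outcome, whereas a likelihood-based model also allows loss that depends on observed values.

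Second, the model line lists two factors but not the term that estimates the treatment effect. Visit 0 precedes the intervention, and so does visit 1 if measurements are taken before the session. A treatment main effect averages those visits in. The paired t test compares time points within women and contrasts no arms.

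At stake are the precision, possible bias and interpretation of the repeated continuous secondary outcomes. The primary outcome, gestational diabetes at 24-28 weeks, is a single binary assessment and is not touched.

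**Working it through.** **The plan's own figure.** The plan gives none for the longitudinal analysis. Its only sample size, 315 per group, is for the binary primary outcome (35% against 24.5%, 80% power, two-sided 0.05). The pooled formula gives 297, or 316 with continuity correction, so 315 is reproduced to rounding. It says nothing about the MANOVA.

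**Inputs.** From the documents: 500 randomised per arm, about 20% drop-out, at least 700 of 1000 assessed (at most 30% lost). Assumed, because the documents give none: SD 1, correlation r between visits, loss at each visit, a post-treatment effect in SD units. Baseline is taken as complete.

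**1. Pre and post only.** Let f be the fraction with a post value. Variances of the arm mean, in units of 1/500, at r = 0.6 and f = 0.7:

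- Complete-case change: 2(1−r)/f = 0.8/0.7 = 1.143.
- Unconstrained mixed model, change: (1−r²)/f + (1−r)² = 0.914 + 0.16 = 1.074.
- Mixed model with common baseline: (1−r²)/f = 0.64/0.7 = 0.914.
- t test on the post value alone: 1/f = 1.429.

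SE ratios:

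- Complete-case change against unconstrained: √(1.143/1.074) = 1.03. With 20% missing it is √(1.000/0.960) = 1.02.
- Complete-case change against common baseline: √(1.143/0.914) = 1.12.
- Post-value t test against common baseline: √(1.429/0.914) = 1.25.

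In the last two ratios f cancels. The first reduces to √(2/(1+r)) and the second to 1/√(1−r²). Those gains come from using the baseline well, not from recovering deleted women. Only the 2% to 3% is due to deletion.

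**2. Four visits with continuing loss.** Take baseline, 24-28 weeks and two later visits, with 30% lost by 24-28 weeks and 10% more at each later visit. Complete cases: 1000 × 0.7 × 0.9 × 0.9 = 567. SE of the arm difference in means at 24-28 weeks:

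- Complete case: √(2/283.5) = 0.084.
- Likelihood, unconstrained: √(2 × (0.64/0.7 + 0.36)/500) = 0.071.
- Ratio: 1.18. Simulation of the same setting gave 0.084 to 0.085 against 0.070 to 0.071, or 19% to 20%.

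On the change scale the ratio is √((0.8/0.567)/1.074) = 1.15 against the unconstrained model and √((0.8/0.567)/0.914) = 1.24 against the common-baseline model. About 20% is a fair summary. Here deletion matters: 700 women have a 24-28 week value and 133 of them are discarded for later absences.

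**3. Which contrast.** With one pre and one post visit and a true post-treatment effect of 0.2 SD, 350 women per arm:

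| r | Main effect (estimates 0.1; person-mean variance (1+r)/2) | Treatment-by-period (estimates 0.2; variance 2(1−r)) | Baseline-adjusted post value (estimates 0.2; variance 1−r²) |
|---|---|---|---|
| 0.3 | 37.5% power | 61% | 79% |
| 0.5 | 33% | 75% | 86% |
| 0.7 | 30% | 93% | 96% |

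At r = 0.5, for example, the main effect has z = 0.1/√(2 × 0.75/350) = 1.53, and Φ(1.53 − 1.96) = 33%.

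**4. Bias.** In the four-visit setting, let control-arm retention depend on the previous value (0.7 log-odds per SD), with a true effect of −0.25. The complete-case arm difference at 24-28 weeks is about −0.48 or −0.02, according to the direction of the dependence. The complete-case difference in change is about −0.20 or −0.30. Likelihood gives about −0.25 each time. In a three-visit setting with control-arm loss depending on the middle visit, the complete-case change was −0.205 at that visit but unbiased at the last. With loss unrelated to outcome there was no bias in change.

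**The case against.** The section sets out to estimate changes between pre- and post-treatment periods and says that interactions will be evaluated. A colleague may fairly read that as treatment-by-period, which is undiluted. This stands. A reader might infer that the planned analysis dilutes the treatment effect, but the documents do not name the main effect as the estimate. What remains is that no sentence names either term.

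The visits entered are not fixed either. A reader might infer a seven-visit model in which any missed visit removes a woman. The wording describes two periods, and the November 2014 addendum limits adherence biomarkers to baseline and 24-28 weeks, in 10% of women. With two periods, deletion costs only 2% to 3% in SE. This also stands, and it is why the size is given by scenario.

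Listwise deletion is nowhere written. It belongs to the classical method, and no routine is named. The expectation of assessing 700 women is a floor, not a forecast. Size and direction of any bias rest on an invented dropout mechanism.

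Finally, the Final statistical analysis section may govern, and its tests delete nobody seen at the visit in question. But it does not say that it replaces the MANOVA, and single-time tests do not estimate the change over time listed as an objective.

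It could also be said that such detail belongs in a statistical analysis plan. Here, however, the Protocol itself states a method and an analysis rule that conflict once data are missing.

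**Conclusion.** The point holds in limited form, for repeated continuous secondary outcomes only. The stated MANOVA, in its classical form, conflicts with the plan's promise to use all available data, and the treatment contrast is left open between a term that would halve a pre/post effect and one that would not.

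The SE cost is about 3% against an unconstrained mixed model with pre and post only, about 12% against a common-baseline model (a baseline-adjustment gain, not recovered women), and about 20% with four visits and continuing loss. These figures assume correlation 0.6 and 30% missing at 24-28 weeks; continuing loss means 10% more at each later visit. Bias is possible if loss depends on outcome and arm; the documents support no size or direction for it.

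Whichever section governs, a mixed model is at least as good. Under the same assumptions the single-time t test has an SE 25% larger than the common-baseline model. The change is worth making, but it is not critical to the trial's main conclusion.

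**What to change.** Replace the MANOVA sentences in Statistical Analysis with a paragraph that states:

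- Repeated continuous outcomes are analysed by a likelihood-based mixed model for repeated measures, using every observed visit of every randomised woman.
- The model contains visit, arm-by-post-baseline-visit terms, a common baseline (or baseline as covariate) and the stratification factors (age, BMI, parity).
- The reported estimate is the arm difference with 95% confidence interval at 24-28 weeks and at each later visit analysed. The visits entered are listed for each outcome.
- Within-arm paired tests are descriptive only.
- For repeated continuous outcomes this paragraph governs over the t and Mann-Whitney tests in Final statistical analysis.

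The cost is one paragraph of wording and a slightly more complex model to report. It needs no new data, visits or patients.
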